#### Questionnaires

Self-report information in the form of a questionnaire will be administered by staff at baseline (pregnancy) and when children are aged 24- and 36-months. The questionnaire was pilot-tested using focus groups comprised of members of participating Indigenous communities and Aboriginal Maternal Infant Care workers, with the questions revisited and refined during Year 1 of the research. Questionnaire items were modelled on those used in both Australian [26] and international population-level surveys [27,28] and include carers’ self-reported ECC experience of their child, as well as carers’ oral health knowledge, oral self-care, dental service utilisation, oral health-related self-efficacy and oral health literacy.

Covariates include socio-demography, oral health and general health. Socio-demographic covariates (collected at baseline only) include age, Indigenous affiliation, residential location, education level, employment, gross household income, house ownership, number of children, number of people who stayed in house the previous night, and car ownership. Oral health covariates include carer self-reported oral health, oral health-related quality of life, and history and experience of dental services of both the parent and child. General health covariates include parent behaviours such as tobacco smoking, alcohol consumption and self-reported general health.

#### Clinical examinations

Information about child clinical oral health status will be collected during standardised examinations conducted at the 24- and 36-months follow-ups by two calibrated dental professionals. Before examination, a new toothbrush will be used to clean the teeth, and the teeth dried with gauze. Examiners will follow a standardised protocol. Procedures appropriate for young children will be used during the examinations, for example, children examined in the ‘knee-to-knee’ position on their carers’ lap. Standard infection control procedures will be followed with a fibre-optic light used as a light source. No sharp instruments will be used during examinations. The status of all teeth and tooth surfaces will be examined and recorded. Non-cavitated and cavitated lesions will be recorded for all teeth. The study will focus on the earliest manifestation of ECC. Two ECC case definitions will be used: (1) one or more upper incisor teeth labial surfaces being carious, either non-cavitated or cavitated and; (2) one or more non-cavitated or cavitated carious, missing of filled surfaces. Lesions will be diagnosed as ‘non-cavitated’ if an area of demineralization is without loss of surface continuity detected visually. Lesions will be diagnosed as ‘cavitated’ if a loss of continuity of the enamel is detected [2]. In addition, levels of tooth loss and dmft/s indices will be assessed from the tooth- and surface-level recorded observations. Diagnosis will be based on visual criteria only.

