## Background

### Early childhood caries (ECC)

Early childhood caries is the presence of one or more decayed, missing, or filled primary teeth in children aged 71 months (5 years) or younger [1]. In children younger than 3 years, any sign of dental decay is considered Severe ECC, or S-ECC [2]. Early childhood caries not only causes pain, but also impacts children’s ability to eat, play and sleep [3]. It is associated with chronic childhood conditions and nutritional disorders [4], and is the strongest predictor of poor oral health later in childhood and into adulthood [5], when it is associated with clinical symptoms as well as psycho-social outcomes such as low self-confidence and poor perceived social acceptability.

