3. Motivational interviewingParticipants in the test-immediate intervention group receive four motivational interviewing (MI) sessions by trained study staff, with each session focussing on a specific directive. For participants in the test-immediate intervention group, the MI sessions occur at baseline (pregnancy) and when the child is aged 6-, 12- and 18-months. The directives for each of these sessions are: (1) Baseline/pregnancy; encourage participants to attend dental appointments; (2) Child aged 6-months; encourage participants to learn more about the importance of non-cariogenic foods and drinks for their child; (3) Child aged 12-months; emphasise to participants the importance of fluoride in early childhood caries prevention; and 4) Child aged 18-months; encourage participants to enrol their child for a dental check. Participants in the control-delayed intervention group receive three motivational interviews when the child is aged 24-, 30-, and 36 months, with the first session combining directives one and two.

4. Anticipatory guidanceAnticipatory guidance (AG) for those in the test-immediate intervention group will occur during pregnancy and when the child is aged 6-, 12-, and 18-months. Participants in the control-delayed-intervention group will receive anticipatory guidance when the child is aged at 24-, 30-, and 36 months. The anticipatory guidance topics reflect and compliment the directives of the MI sessions.

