### Statistical Analysis

Test-immediate and control-delayed intervention groups will be compared at baseline, 24- and 36- months. Results will be compared using the Generalized Linear Mixed Model (GLMM) approach to focus on variation in the primary outcome: early childhood caries levels. All participants who completed the 24-month follow-up ECC-related outcome data will be included in multivariate modelling. Analysis will include fitting GLMM models for analysis of the correlated data in order to determine factors associated with ECC-related changes. Missing data will be addressed by the GLMM estimating mechanism, which assumes interdependence between repeated measures of participants, copes well with random missing data, allows for different intercepts and rates of change, and provides good predictive models. All variables showing associations at p < 0.15 in the GLMM univariate analyses will be entered into multivariate models using a stepwise approach. All effects will be estimated with 95% confidence intervals, with statistical significance taken as a two-sided p-value less than 0.05. This data will contribute to the inter-country analysis.

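### ECC case definition 1 counts only currently carious upper-incisor surfaces, so treated disease scores as no disease, possibly unequally between arms at 24 months

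*Protocol article*

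**What the plan says.** The Background section (Early childhood caries) defines the disease by experience, treated or not: "Early childhood caries is the presence of one or more decayed, missing, or filled primary teeth in children" up to the stated age limit.

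Clinical examinations then gives two case definitions. Definition 1 is "one or more upper incisor teeth labial surfaces being carious, either non-cavitated or cavitated". Definition 2 is "one or more non-cavitated or cavitated carious, missing of filled surfaces". The same section says that the status of every tooth and surface is recorded, and that tooth loss and dmft/s will be derived from those records. Outcomes come from "standardised examinations conducted at the 24- and 36-months follow-ups by two calibrated dental professionals".

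Under Intervention review, item 3, the immediate arm's session at child age 18 months is to "encourage participants to enrol their child for a dental check". For the other arm: "Participants in the control-delayed intervention group receive three motivational interviews when the child is aged 24-, 30-, and 36 months".

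Statistical Analysis names the "primary outcome: early childhood caries levels" and does not say which case definition, if either, carries it.

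**The concern.** Definition 1 is called an ECC case definition but measures something narrower than ECC as the article defines it: caries on the upper incisors that is still untreated at the examination. Filling or extracting a decayed incisor removes the child from the count although no caries was prevented.

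If treatment were equally common in both arms, this would only lower both prevalences. The trial gives a reason why it might not be equal. Before the 24-month examination, one arm is urged to bring the child into contact with dental services and the other is not. If that encouragement leads to treatment, definition 1 shows less ECC in the immediate arm for a reason unrelated to prevention. The error then runs in the direction of the trial's hypothesis, and definition 1 alone could not separate prevention from treatment.

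**Working it through.** **1. How each definition classifies the same child** (no other tooth affected)

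| Upper-incisor labial surfaces at examination | Definition 1 | Definition 2 | Background definition |
|---|---|---|---|
| Cavitated, untreated | case | case | case |
| Some filled, one still carious | case | case | case |
| All affected surfaces filled | **non-case** | case | case |
| All affected incisors extracted for caries | **non-case** | case | case |

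Only the last two rows diverge. They require every affected upper-incisor labial surface to have been treated.

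**2. Timing**

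The dental-check directive is given at 18 months, in the immediate arm only. The age window in the fluoride varnish item runs from one month before target to three months after. If it applies to the whole 18-month meeting, contact falls at 17 to 21 months. An examination held on target at 24 months then follows by 24 − 21 = 3 to 24 − 17 = 7 months. The delayed arm has no session before 24 months.

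**3. Size**

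The article gives neither upper-incisor caries prevalence nor treatment rates, so no stated figure can be reproduced for this point and the inputs below are assumptions. The one figure taken from the article is 125 evaluable children per arm (Sample size). Its baseline inflation does reproduce: 250 / 0.65 = 384.6, rounded up to 385.

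Let p be true upper-incisor caries experience, equal in both arms (no preventive effect). Let f_D and f_I be the shares of affected children, delayed and immediate, whose affected surfaces have all been filled or extracted by 24 months.

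- Observed prevalence under definition 1: p(1 − f_D) and p(1 − f_I)
- Spurious difference: p(f_I − f_D)
- Ratio: (1 − f_I) / (1 − f_D)

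The last column is the chance of a significant result favouring the intervention with 125 per arm. It uses the normal approximation for two proportions at two-sided 0.05, so 2.5% is the nominal value in that direction.

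| p | f_D vs f_I | Observed, delayed vs immediate | Spurious difference | Ratio | Chance |
|---|---|---|---|---|---|
| any | equal | equal | 0 | 1.00 | 2.5% |
| 30% | 0% vs 5% | 30.0% vs 28.5% | 1.5 points | 0.95 | 4.5% |
| 50% | 5% vs 15% | 47.5% vs 42.5% | 5.0 points | 0.895 | 12.2% |
| 50% | 5% vs 25% | 47.5% vs 37.5% | 10.0 points | 0.789 | 35.8% |
| 65% | 5% vs 25% | 61.75% vs 48.75% | 13.0 points | 0.789 | 54.3% |

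Worked line for 50% with 5% vs 15%:

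- Difference: 0.50 × (0.15 − 0.05) = 0.05.
- Pooled proportion 0.45, so the null standard error is √(2 × 0.45 × 0.55 / 125) = 0.0629.
- Unpooled standard error: √((0.475 × 0.525 + 0.425 × 0.575) / 125) = 0.0628.
- z = (0.05 − 1.96 × 0.0629) / 0.0628 ≈ −1.17, and Φ(−1.17) ≈ 0.12.

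If definition 1 also counted filled surfaces and surfaces lost to caries, both observed values would equal p and the spurious difference would be 0 in every row.

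**The case against.** **The two definitions may be meant to complement each other.** The article says that it focuses on the earliest manifestation of ECC, and a current-lesion measure on the upper incisors beside a full-experience measure can serve that. This explains having two measures. It does not excuse the omission: definition 1 already admits cavitated lesions, so it is not confined to early disease, and a filled or extracted incisor was diseased. If untreated lesions are what is meant, the label is wrong.

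**The other outcomes keep treated disease.** This stands. Definition 2, dmft/s and tooth loss would still register the child, and a discrepancy with definition 1 would be visible in the trial's own results. A reader might infer that the primary result is biased. The article does not support that, because it does not tie the primary outcome to definition 1; equally, it does not keep definition 1 out.

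**The causal chain is long.** This also stands. The directive encourages enrolment for a check and delivers no treatment. The immediate arm's dental care component is arranged in pregnancy or within six weeks of birth, so it does not itself provide child restorations before 24 months. The carer must act, the child must attend and be treated, and every affected surface must be dealt with, all in about six months. One remaining non-cavitated lesion keeps the child a case. The larger values in the table need a 20-point difference between arms in complete treatment, and no figure in the article supports that.

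**At 36 months** a reader might infer that reversals from case to non-case corrupt the repeated-measures analysis. That is not shown. A measure of current disease may properly reverse, and the delayed arm has by then begun its own intervention, so even the direction is unclear.

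**The article is condensed.** The standardised examination protocol it mentions may settle how treated incisors are coded. The case definition as published does not.

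**Conclusion.** The definitional gap is certain: definition 1 omits filled and missing surfaces, contrary to definition 2 and to the article's own account of ECC. At 24 months the resulting misclassification can differ by arm. If the 18-month encouragement leads to treatment, it favours the intervention.

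The amount is not known and may be small. The range of 1.5 to 13 points, with a 4.5% to 54% chance of a false significant result in favour of the intervention against 2.5% nominal, rests wholly on assumed caries experience of 30% to 65% and assumed treated shares from 0% vs 5% to 5% vs 25%. It also assumes equal true caries in both arms and 125 children per arm. Equal treated shares give zero. The point is confined to definition 1; no direction can be claimed at 36 months.

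**What to change.** Either of two changes is enough, made before the outcome data are analysed.

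- **Complete definition 1.** Count a child as a case if at least one upper-incisor labial surface is carious (non-cavitated or cavitated), filled, or missing because of caries. Apply this at both the 24- and 36-month examinations.
- **Or relabel it.** Call definition 1 untreated upper-incisor caries, and base the between-arm ECC comparison on definition 2.

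The cost is one line in the outcome definition. No extra examination is needed, because the status of all teeth and surfaces is already to be recorded. The first option needs missing incisors to be attributed to caries or to another cause. If the examination form does not already capture that, it should be added before the 24-month visits.

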### Statistical Analysis

Test-immediate and control-delayed intervention groups will be compared at baseline, 24- and 36- months. Results will be compared using the Generalized Linear Mixed Model (GLMM) approach to focus on variation in the primary outcome: early childhood caries levels. All participants who completed the 24-month follow-up ECC-related outcome data will be included in multivariate modelling. Analysis will include fitting GLMM models for analysis of the correlated data in order to determine factors associated with ECC-related changes. Missing data will be addressed by the GLMM estimating mechanism, which assumes interdependence between repeated measures of participants, copes well with random missing data, allows for different intercepts and rates of change, and provides good predictive models. All variables showing associations at p < 0.15 in the GLMM univariate analyses will be entered into multivariate models using a stepwise approach. All effects will be estimated with 95% confidence intervals, with statistical significance taken as a two-sided p-value less than 0.05. This data will contribute to the inter-country analysis.

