### Aim and hypotheses

This study seeks to determine if implementing a culturally-appropriate early childhood caries (ECC) intervention reduces dental disease burden and oral health inequalities among Indigenous children living in South Australia, Australia. We hypothesize that exposure to a culturally-appropriate ECC intervention will reduce dental disease burden among Indigenous children and reduce oral health inequalities between such children with their non-Indigenous counterparts. The South Australian study described in this paper is part of a larger investigation including research teams in New Zealand and Canada; we will compare findings when they become available.

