## Methods

### Intervention review

In this randomised, controlled trial participants are offered four intervention components: (1) provision of dental care; (2) fluoride varnish application to the teeth of children; (3) motivational interviewing and (4) anticipatory guidance. A schema outlining the study design is presented in Figure 1.

1. Provision of dental careIn the test-immediate intervention group, dental care is arranged during pregnancy or up to six weeks after birth. For participants in the control-delayed intervention group, dental care is arranged when their child is 24 months of age. Care will comprise of extractions, restorations, scaling and prophylaxis and will take as many visits as required to achieve a non-diseased mouth. Participants holding an Australian healthcare or pensioner concession card will be eligible for treatment through the South Australian Dental Service; participants who do not hold this entitlement will receive treatment from private dentists limited to $1265 AUD. Dentists are asked to focus on reducing bacterial load, such as filling or extracting teeth with frank carious lesions. Study staff remind participants of dental appointments by telephoning, sending text messages via mobile phone and sending letters, and attempt to mitigate obstacles such as dental fear and lack of childcare by attending appointments when helpful. Free transport to and from the dentist is also available through culturally-sensitive transport providers.

2. Fluoride varnish applicationsFluoride varnish is applied to children by trained study staff in a setting convenient to participants, often their homes. In the test-immediate intervention group, this occurs when children are aged 6-, 12- and 18-months. Children in the control-delayed intervention group receive fluoride varnish applications at 24-, 30- and 36 months. Given the obstacles in meeting participants, these age targets are extended by one month prior and three months following target age, e.g. the six-month meeting can occur anywhere from five to eight months of age.

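### The primary caries outcome has no visit attached, and only the 24-month group difference tests exposure against no exposure

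*Protocol article*

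**What the plan says.** All references are to the protocol article.

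- **Aim and hypotheses:** the hypothesis is that "exposure to a culturally-appropriate ECC intervention will reduce dental disease burden among Indigenous children".
- **Statistical Analysis:** "Test-immediate and control-delayed intervention groups will be compared at baseline, 24- and 36- months". The primary outcome is the level of ECC, with no visit given. The section continues: "Analysis will include fitting GLMM models for analysis of the correlated data in order to determine factors associated with ECC-related changes". It describes the GLMM as a model for repeated measures that permits different intercepts and rates of change. The multivariate models include everyone with 24-month ECC outcome data.
- **Clinical examinations:** child oral health is recorded at "standardised examinations conducted at the 24- and 36-months follow-ups by two calibrated dental professionals". There is no clinical baseline.
- **Intervention review, immediate arm:** for varnish, "In the test-immediate intervention group, this occurs when children are aged 6-, 12- and 18-months". Motivational interviewing (MI) and anticipatory guidance (AG) also end at 18 months.
- **Intervention review, delayed arm:** "For participants in the control-delayed intervention group, dental care is arranged when their child is 24 months of age", and "Children in the control-delayed intervention group receive fluoride varnish applications at 24-, 30- and 36 months". MI and AG follow the same three ages.
- **Sample size:** the 25 percent difference in ECC prevalence is tied to no visit. Attrition is allowed for up to 36 months.

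**The concern.** In a delayed-intervention design the control arm is a no-intervention control only until its own treatment starts, here at 24 months. A primary outcome with no visit, analysed by a repeated-measures model over two examinations, can yield several group effects: the 24-month difference, the 36-month difference, an effect pooled over both, or a difference in change. These answer different questions, and only the first answers the one in the hypothesis.

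If a pooled, 36-month or change result is taken as the efficacy result, a working intervention can look weaker than it is, because the comparator has been given the same intervention. The section says that the data will also feed the inter-country analysis, so the choice carries beyond this trial.

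**Working it through.** **1. Schedule by target age (Intervention review; Clinical examinations)**

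| | Immediate arm | Delayed arm |
|---|---|---|
| Dental care | pregnancy to six weeks after birth | from 24 months |
| Varnish | 6, 12, 18 months | 24, 30, 36 months |
| MI | baseline, 6, 12, 18 months | 24, 30, 36 months |
| AG | pregnancy, 6, 12, 18 months | 24, 30, 36 months |
| Clinical examination | 24, 36 months | 24, 36 months |

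Sessions with a target age before 24 months, immediate v delayed: varnish 3 v 0, MI 4 v 0, AG 4 v 0. From 24 months and before 36 months: 0 v 2 of each, with a third delayed-arm session due at 36. The varnish item allows a margin ("these age targets are extended by one month prior and three months following target age"), so the last immediate-arm varnish falls at 18 + 3 = 21 months at the latest.

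**2. What each group effect estimates**

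- Difference at 24 months: intervention against none.
- Difference at 36 months: early against delayed start.
- Effect pooled over both visits: a mixture of the two.
- Clinical change: with no clinical baseline it can only run from 24 to 36 months, when the delayed arm is under treatment and the immediate arm's scheduled sessions are over.

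**3. Direction of the effect at 36 months**

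Let p be delayed-arm ECC prevalence at 24 months, i the risk of ECC over the next year in an untreated ECC-free child, and r the relative reduction in that risk from delayed treatment. Assume lesions do not reverse.

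- Delayed arm at 36 months, untreated: p + (1 − p)i
- Delayed arm at 36 months, treated: p + (1 − p)i(1 − r)
- Shift: (1 − p) × i × r

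The shift is positive for any r above zero. It lowers the 36-month difference by that amount whatever happens in the immediate arm.

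**4. Size, on assumed rates only**

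The document gives none of p, i or r. For p of 30 to 69%, i of 20 to 40% and r of 25 to 50%:

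- Low end: 0.31 × 0.20 × 0.25 = 0.0155, about 1.6 points.
- High end: 0.70 × 0.40 × 0.50 = 0.140, or 14.0 points. This takes the extreme of all three inputs at once.

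**5. The plan's own figures, and one example**

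250 / (1 − 0.35) = 384.6, so the stated 385 reproduces. The 250 cannot be confirmed without a control rate. A 25-point absolute difference needs at most about 62 per arm. A 25% relative reduction needs 126 per arm from a control rate of 69% and 121 from 70%, so 125 fits a relative reduction from roughly 69 to 70%.

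Assume, then, 70% v 52.5% at 24 months with 125 per arm, and 30% yearly incidence in immediate-arm children still free of ECC:

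- 24 months: difference 17.5 points, power 0.81.
- 36 months, delayed-arm incidence also 30% (treatment has no effect): 70 + 30 × 0.30 = 79.0% v 52.5 + 47.5 × 0.30 = 66.75%; difference 12.25 points, power 0.59.
- 36 months, delayed-arm incidence cut to 20%: 70 + 30 × 0.20 = 76.0% v 66.75%; difference 9.25 points, power 0.37.

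Delayed treatment accounts for 12.25 − 9.25 = 3.0 points. The rest of the fall from 17.5 would occur without it, because fewer delayed-arm children remain at risk. A simple average over the two visits is (17.5 + 9.25)/2 = 13.4 points, against 17.5 for the contrast that matches the hypothesis. A GLMM would weight the visits differently, so this average is only a guide.

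**The case against.** The strongest reply is that this is a condensed article. A full protocol or analysis plan may name the primary visit and the model terms. The sentence listing baseline, 24 and 36 months may be a list of data-collection points, since no child can have ECC at baseline. The 24-month comparison is planned, and 24 months alone defines who enters the models. The change sentence speaks of associated factors, not of an efficacy test. The arm names already disclose early against delayed start.

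Much of this stands, and it rules out several stronger readings that a reader might infer:

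- **That the plan deliberately gives the two visits equal weight as efficacy tests.** The text does not say so.
- **That the 36-month comparison is invalid.** It is randomised and answers a sound question, just not the one in the hypothesis.
- **That the 24-month comparison is contaminated**, because the window would allow a delayed-arm session at 23 months. The order of examination and session is detail that an article may leave out.
- **That delayed treatment would reverse the direction of the result.** This depends on the rates chosen. With 69% v 51.75% at 24 months, 30% incidence and 25% protection retained in the immediate arm, the 24-to-36-month increase is 0.4825 × 0.225 = 10.9 points (immediate) against 0.31 × 0.30 = 9.3 points in an untreated delayed arm. The immediate arm already rises more before any delayed treatment. With the delayed arm given the same 25% protection, the 36-month difference still favours the immediate arm: 69 + 31 × 0.225 = 76.0% v 51.75 + 10.9 = 62.6%, or 13.4 points.

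The reply does not remove the point itself. The section does fix the primary outcome, the comparison visits and the type of model. In this design the visit decides which question the primary outcome answers. The 24-month inclusion rule says who is modelled, not which effect is primary.

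**Conclusion.** The point holds in limited form. As written, the primary outcome has no visit, and the model spans one examination before the delayed arm's treatment and one after it. A pooled or change-based group effect would not test the stated hypothesis, and any effective delayed treatment makes the 36-month difference smaller than it would be against an untreated control. The direction follows from the schedules, given that delayed treatment works and lesions do not reverse. The size does not follow: the range of about 1.6 to 14.0 points and the power figures rest on assumed rates. The 24-month comparison the trial needs is already planned; it has not been singled out as the one that tests the hypothesis.

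**What to change.** In Statistical Analysis:

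1. Name the between-group difference in ECC at the 24-month examination as the primary test of the exposure hypothesis.
2. Fit group-by-visit terms in the GLMM, so that the 24- and 36-month effects are estimated separately.
3. Report the 36-month difference and the 24-to-36-month change as secondary comparisons of early with delayed start, not as evidence for or against efficacy.

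This adds no participants, visits or measurements. The cost is that 36-month data no longer contribute to the primary exposure test. The 35% attrition allowance runs to 36 months, so if losses accumulate over time the planned numbers at 24 months should be no smaller.

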#### Sample size

Based on a recent ECC intervention study of Australian Northern Territory-dwelling Indigenous children, it was estimated that a sample size of 250 (125 in each arm of the trial) would be necessary to detect a 25 percent difference in ECC prevalence between the two groups, at the significance criterion of 0.05 and a power of 0.80 [15]. The literature indicates that it is reasonable to expect a difference in effect of this magnitude following a motivational interviewing intervention among Indigenous children [16]. Allowing for an attrition rate of 35 percent after 36 months, 385 participants would be necessary at base-line; rounded up to 400 for convenience (200 test-immediate intervention group, 200 control-delayed intervention group).

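### The modelling set is defined by 24-month completion and the GLMM is the only missing-data method, so loss at the 24-month visit goes uncorrected and children examined only at 36 months are dropped

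*Protocol article*

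**What the plan says.** Under Statistical Analysis, the protocol article fixes who enters the model: "All participants who completed the 24-month follow-up ECC-related outcome data will be included in multivariate modelling". It then says "Missing data will be addressed by the GLMM estimating mechanism", and describes this mechanism as one that "copes well with random missing data". It gives no other analysis population and no other missing-data method.

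The Clinical examinations section gives the timing of the outcome: "Information about child clinical oral health status will be collected during standardised examinations conducted at the 24- and 36-months follow-ups". Mothers enrol in pregnancy or within six weeks of birth (Participants and recruitment), so there is no earlier child caries measurement.

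The Sample size section plans for heavy loss: "Allowing for an attrition rate of 35 percent after 36 months, 385 participants would be necessary at base-line", later rounded up to 400.

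Under Intervention review, the immediate arm is offered dental care, interviewing and guidance from pregnancy, with visits at 6, 12 and 18 months. The delayed arm's components start at 24 months.

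**The concern.** A mixed model uses incomplete records only from children who contribute at least one outcome. With caries examined at 24 and 36 months only, and entry tied to the 24-month result, the only outcome that can be missing inside the model is the 36-month one. By then the delayed arm has been offered the intervention. The 24-month visit is the only examination that can compare treated children with not-yet-treated children, and the stated safeguard does not reach it.

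Two groups are affected differently:

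- Children missed at 24 months but examined at 36 are dropped, although the model could use their record.
- Children never examined contribute no outcome under any rule, yet the text reads as if the model dealt with them.

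Planned contact before 24 months is much heavier in the immediate arm, so completion could depend on arm. If it also depends on caries risk, comparing completers no longer preserves the randomised comparison.

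**Working it through.** **1. The plan's own loss figure.** The evaluable number is 250 and attrition is 35% (Sample size). 250 / (1 − 0.35) = 384.6, rounded up to 385, which matches the article. Of 400 randomised, 0.35 × 400 = 140 would be lost and 260 would remain. That exceeds 250, so the allowance protects numbers. The question here is bias.

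**2. Loss at 24 months.** The article gives no 24-month figure. If dropout is constant and reaches 35% at 36 months:

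- counting from birth: 1 − 0.65^(24/36) = 0.250, about 100 of 400;
- counting from four months before birth (assumed): 1 − 0.65^(28/40) = 0.260, about 104 of 400.

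Dropout by 24 months is therefore at most 35%, and about 25-26% under constancy. Single missed visits would add to this.

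**3. What the GLMM can use.**

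| Examined at 24 months | Examined at 36 months | Under the stated rule | What the model could do |
|---|---|---|---|
| yes | yes | in | uses both |
| yes | no | in | covers the missing 36-month result |
| no | yes | out | could use the 36-month record |
| no | no | out | no outcome to use |

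The rule itself costs only the third row, whose size the article does not give. The fourth row needs imputation or weighting.

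**4. Illustration of bias.** None of these inputs is in the article. Assume true 24-month prevalence of 68% (delayed) and 51% (immediate), a relative reduction of 25% (0.68 × 0.75 = 0.51) and a difference of 17 points. Let m be the fraction missing and R the ratio of prevalence in missing to observed children. Then:

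observed prevalence = true prevalence / ((1 − m) + m × R)

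With 40% missing in the delayed arm and 30% in the immediate arm:

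- R = 1.2 in both arms: 0.68 / 1.08 = 0.630 and 0.51 / 1.06 = 0.481; difference 14.8 points.
- R = 1.3 in both arms: 0.68 / 1.12 = 0.607 and 0.51 / 1.09 = 0.468; difference 13.9 points.
- R = 1.3 in the delayed arm only: 0.607 − 0.510; difference 9.7 points.
- R = 1.3 in the immediate arm only: 0.680 − 0.468; difference 21.2 points.

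The 40% and 30% average to the 36-month ceiling. With 25% missing in each arm, closer to step 2, R = 1.3 in both arms gives 0.17 / 1.075 = 15.8 points. R = 1.3 in the delayed arm only gives 0.68 / 1.075 − 0.51 = 12.3 points.

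**The case against.** **The two sentences are compatible.** A reader might infer that the entry rule and the missing-data claim contradict each other. They do not: a child with a 24-month result and no 36-month result stays in, and the GLMM covers the gap. What stands is that the claim is broader than the model can deliver.

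**The rule does not exclude a third of the trial.** A reader might infer this from the 35%. That figure is attrition by 36 months, and children never examined have no outcome under any rule. The rule removes only those seen at 36 but not at 24 months.

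**The sentence does not say that others are left out.** The comparison of arms at each time point is a separate sentence without the restriction, and the modelling is partly described as a search for factors associated with caries change. This is fair, but it is the only population given for the model and a completers set is its natural reading.

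**Completers can be unbiased.** If missingness depends only on arm and on covariates held in the model, no correction is needed. This is right in principle. However, covariates enter by stepwise selection from p < 0.15, so the plan does not secure that condition.

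**Differential loss is conjecture.** Delayed-arm families become eligible for free dental care at 24 months, and both arms receive a gift card for each questionnaire, so attendance could favour either arm. This stands, and it is why no direction of bias is claimed.

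**A separate analysis plan may add imputation and sensitivity analyses.** Their absence from a condensed article is not the point. The point is the population that the article does fix, and the reach it claims for the GLMM.

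**Conclusion.** The point holds in a limited form and should be fixed. As written, the model takes in children with 24-month caries data, and its only missing-data method cannot act on loss at that visit. Children examined only at 36 months are dropped without need.

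The size of any bias cannot be read from the article, which gives no control prevalence, no 24-month loss, no loss by arm and no information on who is lost. In the assumed scenarios with 40% and 30% missing, a true 17-point difference appears as about 14 to 15 points when missing children have 1.2 to 1.3 times the observed prevalence in both arms. It appears as 9.7 points when this holds (at 1.3) in the delayed arm only, and as 21.2 points when it holds in the immediate arm only. Lower loss shrinks these shifts. A reader might infer that the plan will understate the effect, or that the rule alone could create or hide it; the documents support neither reading.

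**What to change.** Replace the entry rule and narrow the missing-data claim:

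- Analyse all randomised participants in their assigned arm.
- Enter every child with a caries examination at 24 or 36 months, with an arm-by-visit term so that the 24-month contrast is estimated separately.
- Handle missing 24-month caries by multiple imputation within arm, or by inverse-probability weighting, using recruitment site and the baseline questionnaire covariates. Use the 36-month examination for imputation only within arm, because in the delayed arm it follows the start of the intervention.
- Add a sensitivity analysis in which missing children depart from missing at random by an amount that may differ by arm.
- Keep the 24-month completers as a sensitivity set.
- Do not state that the GLMM addresses children with no outcome.

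The cost is revised wording and some extra programming. Site and the baseline covariates are already collected, so no new data are needed. Imputation and weighting bring assumptions of their own, which the arm-specific sensitivity analysis is there to test.
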